## Abstract

**Background:**

Practitioners of traditional Chinese medicine know that auricular point acupressure (APP) using vaccaria seeds on the large intestine point (CO7) has a significant effect on postoperative gastrointestinal dysfunction. A standardized, clinical, research design will transform this clinical experience into scientific evidence, thus providing a basis to promote the wider use of this therapy. We aim to carry out a double-blind, randomized, controlled trial (RCT) to evaluate the efficacy and safety of APP treatment for gastrointestinal dysfunction after laparoscopic cholecystectomy.

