### Outcome measures and participant timeline

#### Outcome measures

Baseline dataDemographic data will be recorded using a general information questionnaire, which we designed in house. The questionnaire includes questions on age, gender, education, occupation, weight, and height.Clinical characteristics will be recorded using another in-house-designed questionnaire. Specifically, data will be collected on the surgery time, anesthesia time, intraoperative blood loss, intraoperative fluid transfusion volume, and vital signs (temperature, heart rate, respiratory rate, and blood pressure).Primary outcome measureThe primary outcome is the time to first passage of flatus—we will begin observing and recording when subjects return safely to the ward, and the subjects and their families will be asked to record the time of the first passage of flatus. The interval between the two time points will be then calculated.Secondary outcome measuresTime to first defecation: We will observe and record when the subjects return safely to the ward, and the subjects and their families will be asked to record the time of first defecation. The interval between the two time points will then be calculated.Abdominal pain: The subjects’ degree of postoperative pain will be assessed using the VAS scale [10]. The first evaluation will be performed 6 h after surgery, immediately before the first treatment. Evaluations will then be carried out once every 12 h, for seven evaluations. Assistance will be given to subjects and their families in recording this information.Abdominal distention: The Likert scale will be used to assess the subjects’ degree of postoperative abdominal distention [11]. The first evaluation will be performed 6 h after the surgery, immediately before the first treatment. Evaluations will then be carried out once every 12 h, for seven evaluations. Assistance will be given to subjects and their families in recording this data.Nausea: The VAS scale will be used to assess subjects’ degree of postoperative nausea [10]. The first evaluation will be performed 6 h after the surgery, immediately before the first treatment. Evaluations will then be carried out once every 12 h, for seven evaluations. Assistance will be given to subjects and their families in recording this data.Vomiting: The frequency of postoperative vomiting will be recorded. The first evaluation will be performed 6 h after the surgery, immediately before the first treatment. Evaluations will then be carried out once every 12 h, for seven evaluations. Assistance will be given to subjects and their families in recording this data.Mental status: The Hospital Anxiety and Depression Scale (HADS) will be used to assess the subjects’ postoperative mental status [12]. The HADS consists of 14 items: seven assess depression, and the other seven assess anxiety. The scores of the anxiety and depression subscales are classified as follows: 0–7 points indicate no symptoms, 8–10 points indicate suspected symptoms, and 11–21 points indicate confirmed symptoms. The first evaluation will be performed 24 h before surgery, and the second evaluation will be performed on the day of discharge.Quality of life: the Gastrointestinal Quality of Life Index (GIQLI) will be used in this study [13]. The GIQLI aims to measure the quality of life of subjects with digestive diseases and includes five domains: subjective symptoms, physiological functional status, daily life, social activities, and psychological and emotional state. Within these domains, 36 items are assessed, each with a score from 0 to 4 points, for a total possible score of 144 points. The normal population will score 12–125 points. The first evaluation will be performed 24 h before surgery, and the second will be conducted 2 weeks after discharge. A follow-up evaluation will be carried out 1 month after discharge. Higher scores indicate better health status.Safety indicatorsAn event can be defined as an adverse event if at least four subjects suffer a symptom—such as local skin allergies, dizziness, and low blood sugar—during the treatment-evaluation period. These events will be statistically analyzed, and treatment safety is evaluated on this basis, in accordance with the research protocol. If serious adverse events occur, they will be immediately reported and managed accordingly.Participant timelineFor a complete overview of the time schedule of enrollment, interventions, and assessment for participants, see Fig. 4.

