#### Statistical analysis

Content of statistical analysisSample distribution: The absolute number of dropouts as well as the rate will be described for each data set. These data will be analyzed, and the reasons for each termination are listed in detail.Balance comparison: The subjects’ general information will be compared to assess the comparability of the two groups.Efficacy analysis: The subjects’ time to first passage of flatus will be used as the primary outcome measure to evaluate the efficacy and safety of APP in treating gastrointestinal dysfunction after laparoscopic cholecystectomy. The means and standard deviations will be calculated to describe the outcome measure, and the experimental and control groups will be statistically compared using two independent-sample *t* tests. The subjects’ time to first defecation, abdominal pain, abdominal distention, nausea, vomiting, mental status, and quality of life—i.e., the seven secondary outcome measures—will be used to evaluate the efficacy of the APP. Six of these—namely, the time to first defecation, abdominal pain, abdominal distention, nausea, vomiting, and quality of life—will be described using mean ± standard deviation. The scores for mental status will be recorded and categorized in terms of the classification criteria. The statistical analysis of time to first defecation is the same as that of time to first passage of flatus; abdominal pain, abdominal distention, nausea, vomiting, and quality of life will be statistically compared between groups using Repeated Measures Analysis of Variance (RMANOVA). However, before the RMANOVA is performed, a sphericity test will be used to determine whether the data are suitable for analysis using RMANOVA. If the data do not meet the conditions of sphericity, the correction factor *ε* will be used to correct the degree of freedom before the RMANOVA is performed. The categorical measure of mental status will be analyzed using either the rank-sum test or Spearman’s rank correlation.Safety analysis: In accordance with the above definitions of adverse events, we compiled a list describing, grading, and explaining the adverse events in detail. We will ascertain descriptive statistics of the absolute number—as well as the incidence—of each adverse event in both groups. When making comparisons, we will use the *χ*^2^ test or Fisher’s exact test for statistical analysis.Methods of statistical analysisData will be analyzed in accordance with the principle of intention-to-treat (ITT). That is, we will include all subjects who were treated at least once in the trial. Efficacy and safety measures will be analyzed in accordance with “per-protocol” (PP), whereby we will include all subjects who completed the entire trial and followed the protocol requirements. Quantitative variables in the trial data will be expressed as $$ \overline{\mathrm{X}}\pm \mathrm{S}\mathrm{D} $$ for statistical description, whereas qualitative variables will be recorded as the number of cases in each category. If the quantitative variables constitute repeated measures data, then RMANOVA will be used for comparison, and the sphericity test will be used to determine the suitability of, as well as to correct, the data. Qualitative variables will be analyzed using either the rank-sum test or Spearman’s rank correlation; count data for incidence will be compared using the *χ*^2^ test or Fisher’s exact test. All statistical tests are two-sided, and differences with *P* values < 0.05 will be considered statistically significant. Statistical analysis will be performed using SPSS 19.0 statistical software for calculations.

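### A non-serious symptom counts as an adverse event only once at least four subjects have it, so harms seen in one to three subjects drop out of the safety result

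*Protocol article*

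**What the plan says.** The safety indicators paragraph under Outcome measures (Protocol article) states that an event "can be defined as an adverse event if at least four subjects suffer a symptom" during the treatment and evaluation period, with examples "such as local skin allergies, dizziness, and low blood sugar". It goes on: "These events will be statistically analyzed, and treatment safety is evaluated on this basis".

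The safety analysis under Statistical analysis refers back to this rule: "In accordance with the above definitions of adverse events, we compiled a list describing, grading, and explaining the adverse events in detail". It then promises "descriptive statistics of the absolute number—as well as the incidence—of each adverse event in both groups", compared by a chi-square or Fisher's exact test.

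Serious adverse events are treated separately: "If serious adverse events occur, they will be immediately reported and managed accordingly". No count is attached to that sentence.

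The article nowhere says that a non-serious symptom in one, two or three subjects will be listed or counted. It also does not say whether the four subjects are to be found in one arm or in the two arms together. Safety is part of the stated aim, which is "to evaluate the efficacy and safety of APP treatment for gastrointestinal dysfunction after laparoscopic cholecystectomy".

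**The concern.** An adverse event happens to one person. Under this rule, whether a subject's dizziness is an adverse event depends on how many other subjects were dizzy. The condition is a raw count with no arm and no denominator. In a trial of 50 that count is not small: four subjects are 16% of an arm of 25 (4/25) or 8% of the whole trial (4/50).

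Because the list, the incidence and the test all follow the same definition, the loss is not confined to one table. A symptom that occurred in three APP subjects and in nobody on sham would not qualify, although 3/25 is 12% (exact 95% confidence interval 2.5% to 31.2%). The trial could then report that no adverse events occurred when some did, in a study meant to support wider use of the therapy.

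**Working it through.** **Inputs from the article**
- Threshold: four subjects (Outcome measures).
- Arm size: 25 randomized per arm, from 21 per arm before a 15% dropout allowance (Sample size estimation).
- Analysis set: Statistical analysis says that safety measures are analysed per protocol, so about 21 per arm is also relevant (25 × 0.85 = 21.25).

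**The plan's own sample size**
- n = (1.96 + 0.84)² × (3.14² + 5.58²) / 4² = 7.84 × 40.996 / 16 = 20.09, rounded up to 21.
- 21 / 0.85 = 24.7, rounded up to 25 per arm and 50 in total. This reproduces, so 25 and 21 are sound inputs.

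**Assumed input.** The article gives no adverse event rates. I take a true APP rate of 10% as the main case and show others.

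**Case A: no cases on sham, or the four are counted within the APP arm.** The symptom fails the definition if X ≤ 3, where X is binomial(N, p):

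P(X ≤ 3) = Σ C(N, x) pˣ (1 − p)ᴺ⁻ˣ for x = 0 to 3.

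- N = 25, p = 0.10: 0.0718 + 0.1994 + 0.2659 + 0.2265 = 0.764.
- N = 21, p = 0.10: 0.1094 + 0.2553 + 0.2837 + 0.1996 = 0.848.

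| True APP rate | 25 per arm | 21 per arm |
|---|---|---|
| 5% | 96.6% | 98.1% |
| 10% | 76.4% | 84.8% |
| 15% | 47.1% | 61.1% |
| 20% | 23.4% | 37.0% |

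The chance of failing the definition drops to 50% only at a true rate of about 14.5% (25 per arm) or 17.2% (21 per arm).

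Part of this is simply that no case occurs. At 10% with 25 per arm, the chance that one to three real cases occur and none counts is 0.764 − 0.072 = 0.692 (73.9% with 21 per arm).

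**Case B: the four are counted over both arms.** With A cases on APP and B on sham,

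P(A + B ≤ 3) = Σ P(A = a) × P(B ≤ 3 − a) for a = 0 to 3.

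For 25 per arm, APP 10% and sham 5%: 0.0718 × 0.9659 + 0.1994 × 0.8729 + 0.2659 × 0.6424 + 0.2265 × 0.2774 = 0.477.

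| Sham rate (APP 10%) | 25 per arm | 21 per arm |
|---|---|---|
| 0% | 76.4% | 84.8% |
| 2% | 64.8% | 75.8% |
| 5% | 47.7% | 61.2% |
| 10% | 25.0% | 38.4% |

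**Without the threshold.** At a 10% APP rate, at least one APP case is recorded with probability 1 − 0.9²⁵ = 92.8% (25 per arm) or 1 − 0.9²¹ = 89.1% (21 per arm).

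**The case against.** The wording is loose (the event *can* be so defined), and monitoring does not wait for a fourth case. The Experimental group section acts on signs in a single subject. Data collection puts adverse events on the case report form, and Quality control has inspectors check adverse event records. Serious events are reported at once. All of this stands, and it limits the defect to how non-serious symptoms are classified and reported. It does not remove the defect, because no other definition is given and the safety analysis rests on this one.

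The size is also open to challenge. A reader might infer that a 10% harm from APP usually disappears whatever happens on sham. The article does not support that. The rule names no arm, so a count over both arms is its literal reading, and the named symptoms can occur on sham. Both arms receive seeds and adhesive tape, have general anaesthesia and surgery, and fast. The article itself links low blood sugar partly to long fasting before surgery. With pooled counting the loss can fall to 25%.

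For the same reason, a reader might infer a bias toward APP because the lost events arise only under pressing. That is not shown; adhesive allergy, for one, does not need pressing.

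A reader might also infer that every printed incidence must be zero or at least 8% or 16%. That fails for figures given per arm: under pooled counting, 3 v 1 qualifies and prints 12% v 4%.

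Finally, the rule is a definition, not an acceptance limit for harm, and nothing in the article says that a non-significant Fisher test will be read as proof of safety.

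**Conclusion.** Wrong as written. Followed literally, the plan leaves non-serious symptoms seen in one to three subjects out of the adverse event list, the incidence and the comparison, and it leaves the counting unit undefined.

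How often a real harm is lost depends on assumed rates. For a symptom at 10% under APP, it is usual (76% to 85%) only if sham has no cases or the count is taken within the APP arm. Under pooled counting with 25 per arm it runs from 65% down to 25% as the sham rate rises from 2% to 10%. That such symptoms would be printed as 0% is an inference from the definition; the article says only which events are analysed.

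The primary analysis of time to first flatus is not affected.

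**What to change.** In the safety indicators paragraph, delete the four-subject condition and define an adverse event as any untoward symptom or sign in an individual subject. Record each one on the case report form. In the safety analysis, list every event by arm with the number of subjects and the percentage; an exact 95% confidence interval is optional. The question of whether to count per arm or over both arms then falls away.

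The cost is a wording change and a longer safety table, with counts that may look less favourable. It needs no extra patients. One limit should be stated in the report: Trial status says that recruitment is ongoing, and the article does not say that the form has captured isolated symptoms so far, so events before the change may be incomplete.

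### At 25 per arm, the safety evaluation should rest on interval estimates for all events, because the only inferential method stated is a chi-square or Fisher test whose non-significance cannot support safety

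*Protocol article*

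**What the plan says.** Safety is a declared aim: the Abstract states that the trial is "to evaluate the efficacy and safety of APP treatment for gastrointestinal dysfunction after laparoscopic cholecystectomy". Under Outcome measures, in the safety indicators, a symptom is defined as an adverse event if at least four subjects have it. The article then says "These events will be statistically analyzed, and treatment safety is evaluated on this basis, in accordance with the research protocol". Serious adverse events are to be reported immediately, separately from this.

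The safety part of Statistical analysis says "we compiled a list describing, grading, and explaining the adverse events in detail", and continues: "We will ascertain descriptive statistics of the absolute number—as well as the incidence—of each adverse event in both groups". For comparisons it names the chi-square test "or Fisher’s exact test for statistical analysis". The general rule reads: "All statistical tests are two-sided, and differences with *P* values < 0.05 will be considered statistically significant". The same section assigns the safety measures to the per-protocol set.

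The Sample size estimation section uses time to first flatus only: 21 per arm, raised to 25 for dropout, 50 in total. It states no harm rate, margin, interval or upper limit.

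**The concern.** The article ties the evaluation of safety to the statistical analysis of adverse events, and the one inferential element in that analysis is a significance test. With 25 per arm such a test rarely detects a moderate excess of local skin reactions, dizziness or low blood sugar, which are the article's own examples. Counts and incidences will be shown, but nothing planned tells the reader how uncertain they are. The trial is meant to support wider use of the therapy on both efficacy and safety. A report of no significant difference in adverse events would add almost nothing to the second of these, while an interval from the same counts would show what has and has not been excluded.

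**Working it through.** **Inputs from the article.** 25 per arm enrolled, 21 evaluable; two-sided 0.05; chi-square or Fisher; SDs 3.14 and 5.58 h; difference 4 h; 15% dropout. **Assumptions.** All harm rates, since the article gives none; a range is shown.

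**1. The plan's own figure.** n = (1.96 + 0.84)² × (3.14² + 5.58²) / 4² = 7.84 × 40.996 / 16 = 20.09, so 21; 21 / 0.85 = 24.7, so 25 per arm. It reproduces, and no safety quantity enters it.

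**2. What significance requires with no sham events, 25 per arm.**
- Fisher, k v 0: P = 2 × C(25,k) / C(50,k). For k = 5, 2 × 53,130 / 2,118,760 = 0.0502. For k = 6, 2 × 177,100 / 15,890,700 = 0.022. At least 6 v 0 is needed, that is 24% v 0%.
- Uncorrected chi-square, 4 v 0: pooled rate 4/50 = 0.08; statistic = 0.16² / (0.08 × 0.92 × 2/25) = 4.35, P = 0.037. At least 4 v 0 is needed.

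**3. Power.** With a sham rate of 0, power is P(X ≥ 6) for Fisher and P(X ≥ 4) for chi-square, with X binomial (25, p). With a non-zero sham rate, the probabilities of all significant 2×2 tables in the harm direction are summed.

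| True rate, APP v sham | Fisher power | Fisher miss | Chi-square power | Chi-square miss |
|---|---|---|---|---|
| 10% v 0 | 3.3% | 97% | 23.6% | 76% |
| 15% v 0 | 16.2% | 84% | 52.9% | 47% |
| 20% v 0 | 38.3% | 62% | 76.6% | 23% |
| 25% v 0 | 62.2% | 38% | 90.4% | 10% |
| 15% v 5% | 7.2% | 93% | 21.2% | 79% |
| 20% v 5% | 19.8% | 80% | 38.2% | 62% |
| 25% v 5% | 37.0% | 63% | 55.5% | 45% |

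With 21 per arm, Fisher power at 10%, 15%, 20% and 25% v 0 is 5.2%, 19.7%, 41.4% and 63.3%. At 25 per arm Fisher reaches 80% power only at about 30% v 0, 39% v 5% or 49% v 10%. By the usual normal approximation, 80% power for 20% v 5% needs 76 per arm, or 88 with continuity correction.

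**4. What intervals would show from the same counts, 25 per arm.**
- 0/25: two-sided 95% upper limit 1 − 0.025^(1/25) = 13.7%. With 0/21 it is 16.1%.
- 3/25 v 0/25: Fisher P = 0.23; Newcombe 95% interval for the difference −3 to +30 points.
- 5/25 v 0/25: Fisher P = 0.0502, formally not significant; interval +3 to +39 points.

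**5. The four-subject threshold.** With a true rate of 10% under APP and none under sham, the chance of three or fewer affected subjects is P(X ≤ 3) = 76%; at 5% it is 97%. The threshold leaves the power figures above unchanged, because every significant table at this size already has at least four events. It matters for estimation: if events below the threshold are dropped, an apparent 0/25 could hide up to three affected subjects.

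**The case against.** A reader might infer that the plan will declare the therapy safe whenever P exceeds 0.05. The article does not support that. It contains no such decision rule; the 0.05 sentence is the general level for all tests and is not framed as a safety criterion. Nor are the tests the whole of the safety evaluation: a graded list, counts and incidences by arm, and separate reporting of serious events are also planned, and the tests apply when comparisons are made.

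Nor can it be said flatly that the planned tests miss most relevant harms. The article defines no relevant harm, and the miss rate depends on the assumed rates and on the test. Uncorrected chi-square, which the wording permits, detects 20% v 0 in 77% of trials, although sparse cells would usually lead to Fisher.

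It is also fair that sizing on the efficacy outcome alone is normal, that this is labelled a pilot, and that a missing interval may simply have been left to a fuller document. These points stand, and they limit the finding. What remains is that the article names a test as its only inferential method and evaluates safety on that analysis. An analysis plan that followed the article would inherit this weakness. Against a 5% sham rate, both permitted tests miss a 10- to 15-point excess in well over half of trials.

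**Conclusion.** The point holds as an inexpensive improvement. With 25 per arm, a non-significant chi-square or Fisher test cannot support a conclusion about safety. Over the assumed rates of 10% to 20% v 0 and 15% to 25% v 5%, Fisher misses 62% to 97% of true excesses and uncorrected chi-square 23% to 79%. With no events at all, the data exclude only rates above about 14%.

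The size rests on assumed harm rates and on 25 analysed per arm; the per-protocol set would bring the number toward 21. Very large harms, around 30% v 0, would be detected about 80% of the time even by Fisher. The primary efficacy analysis is not affected.

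**What to change.** In the safety indicators under Outcome measures and in the safety part of Statistical analysis, base the safety conclusion on estimation:

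- For every adverse event, in all treated subjects and whether or not four subjects have it, give the number and percentage by arm with an exact 95% confidence interval.
- Give the APP-minus-sham risk difference with a 95% confidence interval (exact or score-based).
- Keep any test P value as supplementary, and state that P > 0.05 will not be taken as evidence of safety.
- Word the conclusion by the upper limit; for example, 0/25 events excludes only rates above about 14%.

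The cost is a few sentences and intervals computed from data already collected, with no extra subjects. Events below the four-subject threshold and subjects outside the per-protocol set must be kept in the safety tables, otherwise the intervals mislead. The downside is a more modest safety statement.
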